### **4.5. IMPACT EVALUATION**

Clinical and economic outcomes will be collected as part of ACT PRIME. In addition, the intervention may have wider expected and unexpected impacts at the household level, community level, private sector level, and public health system level. We propose to evaluate the impact of the intervention amongst community members, health workers and others involved in providing health services using IDIs and FGDs.

#### **4.5.1. Assessment of hypothesised impacts**

Some impacts may be hypothesised in advance based on the predicted and potential mechanisms of change resulting from the intervention as described under 'intended effects' in the logic model (Figure 4.2). Both quantitative and qualitative methods will be used to assess these impacts. For quantitative measurements, existing data collection methods used in ACT PRIME will be utilized wherever possible including cross-sectional survey questionnaires, cohort household surveys, patient exit interviews, health worker knowledge questionnaires, and health facility surveillance questionnaires.

For qualitative assessments of intended effects, IDIs and FGDs will be used to assess whether and how the intervention affected specific hypothesised impacts. IDIs will be conducted with implementers and health workers in the HFI arm, and FGDs will be conducted with primary caregivers.

#### **4.5.2. Assessment of undetermined impacts**

Unexpected impacts will be assessed through a 'most significant change' (MSC) evaluation. MSC is a participatory evaluation technique that aims to collect and systematically analyse significant changes from the perspectives of those involved in a programme [41]. The technique aims to capture the values and perspectives of respondents, aiming to enrich the understanding of the intervention beyond intended changes and pre-defined indicators. A sample line of MSC questions include, "Looking back over the past three months what do you think was the most significant change in the way you managed illness in your household? Why is this significant to you? What difference has this made now or will it make in the future?" We will collect MSC stories from participants and use traditional qualitative data analysis approach to display the diversity and richness the responses. The MSC questions will be asked at the start of FGDs and IDIs that will then go on to ask directly about hypothesized impacts.

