#### Introduction to in-depth interview

*“Hello, my name is ..... I am interested in interviewing you. I would like you to express your own views and experiences about your perspectives on the implementation of the ACT PRIME health facility intervention to improve the health of children in Tororo by improving services at government-run health facilities. A note-taker will be writing down what you say for our records, and we will record the interview using a digital recorder; these notes will be kept securely and your name will not be used anywhere. Your answers will be looked at together with those of many other implementers and you will not be identifiable in any reports that are published.*

*It is very important for us to hear your views and experiences because you have experience implementing the intervention and can give us this insight. We hope you will have time to spend with us now to complete this interview. The interview will take about 45 minutes; but if you prefer we can reschedule the interview for tomorrow or another day of your convenience.*

*Do you have any questions? Do you agree to continue before we start?*

*Now we request that we all switch off our mobile phones so that we are not distracted.”*

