| 1. Role of the implementer          | a) What has been your role as an implementer of this intervention?                                                                                                                                                                                                                                                                                                                                                                                                                                                                                                                                                                                                                                                                                                                           |
| 2. Meeting participant expectations | 
a) What do you think participants expected from the health facility intervention?
 
b) Do you think this intervention met their expectations? Probe: What expectations were met and what else happened that you think they were not expecting?
                                                                                                                                                                                                                                                                                                                                                                                                                                                                                                                            |
| 3. Implementation Process           | 
a) In your opinion, was the training component of the HFI implemented as planned? Probe for specifics, why?
 
b) In your opinion, was the information management component of the HFI implemented as planned? Probe for specifics, why?
 
c) In your opinion, was the supply of consumables including malaria diagnostics and antimalarial drugs component of the HFI implemented as planned? Probe for specifics, why?
 
d) Looking back over the past two years, what component of the intervention do you think was most successfully implemented? Probe for specifics.
 
e) Looking back over the past two years, what component of the intervention do you think was least successfully implemented? Probe for specifics.
 |

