#### Introduction to in-depth interview

*"Hello my name is \_\_\_\_\_ and I am interested in interviewing you. This interview will ask you to express your own views and experiences about your work and role at this health centre. We are interested in knowing whether improving the health services at this health centre has improved children's health in this area. We are specifically asking you about the ACT PRIME study activities which include 1) health center management training, 2) information management, 3) health worker training in fever case management and patient-centered services, and 4) supply of consumables, including malaria diagnostics and antimalarial drugs.*

*A note-taker will be writing down what you say for our records, and we will record the interview using a digital recorder; these notes will be kept securely and your name will not be used anywhere. Your answers will be looked at together with those of many other health workers from different facilities and you will not be identifiable in any reports that are published.*

*It is very important for us to hear your views and experiences because you have experience working here and can give us this insight. We hope you will have time to spend with us now to complete this interview. The interview will take about 45 minutes; if you prefer we can reschedule the interview for tomorrow or another day of your convenience.*

*Do you have any questions? Do you agree to continue before we start?*

*Now we request that we all switch off our mobile phones so that we are not distracted."*

| PART 2: IN-DEPTH INTERVIEW – HEALTH WORKERS (HFI) (1)                                                                |                                                                                                                                                           |
|-----------------------------------------------------------------------------------------------------------------------------|-----------------------------------------------------------------------------------------------------------------------------------------------------------|
| Domains, topic questions, and probes: Use the table below to help you administer the questions during the interview. |                                                                                                                                                           |

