**PART 2: STAKEHOLDERS IN-DEPTH INTERVIEW (1)**

**Domains, topic questions, and probes:** Use the table below to help you administer the questions during the interview.

| Domain                              | Topic and Probes                                                                                                                                                               |
|-------------------------------------|--------------------------------------------------------------------------------------------------------------------------------------------------------------------------------|
| 1. Description of job        | a) Can you briefly describe your roles and responsibilities in your job?                                                                                                       |
|                                     | b) What specific role do you play in malaria-related programmes?                                                                                                               |
|                                     | c) Can you describe your involvement, if any, with the implementation of the ACT PRIME health facility intervention?                                                           |
| 2. Significant changes       | a) Looking back over the past year, what do you think is the most significant change in the way illnesses are managed in the area?                                             |
|                                     | b) Why is this significant to you?                                                                                                                                             |
|                                     | c) What difference has this made now or will it make in the future?                                                                                                            |
| 3. Changes in HFI components | a) Can you describe any actions taken to improve the staffing gaps at health centres in the area? Probe: actions taken for all health centres or only some? Which ones? |
|                                     | b) Can you describe any changes to how drugs are re-stocked at health centres in the area? Probe: changes in all health centres or only some? Which ones?               |

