**PART 3: FGD TOPIC GUIDES (1)**

**Domains, topic questions, and probes:** Use the table below to help you administer the questions during the interview.

*'Now I am going to introduce some topics one at a time about your experiences when your children are unwell, and I hope you can discuss them together.'*

| Domain                                               | Topic and Probes                                                                                                                                                                                                                                     |
|------------------------------------------------------|------------------------------------------------------------------------------------------------------------------------------------------------------------------------------------------------------------------------------------------------------|
| 1. Common illnesses in children < 15 years | a) What illnesses have been common in children under 5 years here for the last few months? (Make a list, don't spend too long on this question)                                                                                               |
|                                                      | b) What illnesses have been common in children aged between 5 and 15 years here in the last few months?                                                                                                                                              |
| 2. Sources of treatment and provider roles    | a) In your experience, what sources have been most successful at treating these different illnesses? (Start with malaria. Probe for different medicine, provider, and treatment types)                                                        |
|                                                      | b) What is it about each of these different sources of treatment that is important to you? (e.g. cost, expertise, interpersonal skills, etc. Probe for each source listed and for why different things are important for different illnesses) |
| 3. Significant events                         | a) Looking back over the past three months what do you think was the most significant change in the way you managed illness in your household?                                                                                                       |

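### Section 4.5.2 puts the most-significant-change questions at the start of interviews and discussions, but the implementer guide omits them, two other interview guides name PRIME first, and the caregiver guide asks them third

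*Supplement*

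**What the plan says.** Section 4.5.2 gives the role of the technique: "Unexpected impacts will be assessed through a 'most significant change' (MSC) evaluation". It describes MSC as reaching past intended changes and pre-set indicators, and it fixes the sequence: "The MSC questions will be asked at the start of FGDs and IDIs that will then go on to ask directly about hypothesized impacts".

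Section 4.5.1 names the interviews and discussions that will probe hypothesised impacts: "IDIs will be conducted with implementers and health workers in the HFI arm, and FGDs will be conducted with primary caregivers". Table 4.1 also assigns the stakeholder interviews and the community health worker (CHW) focus groups to the impact evaluation. Secondary objective 4 (section 3.2) covers both expected and unexpected impacts.

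The guides in the appendices open as follows.

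- **Implementers (Appendix Q).** The introduction asks for "your perspectives on the implementation of the ACT PRIME health facility intervention to improve the health of children in Tororo", and the first question is "What has been your role as an implementer of this intervention".
- **HFI health workers (Appendix R).** The introduction says "We are specifically asking you about the ACT PRIME study activities which include" and then lists four activity areas.
- **Key stakeholders (Appendix S).** Item 1c asks "Can you describe your involvement, if any, with the implementation of the ACT PRIME health facility intervention". MSC is domain 2.
- **Primary caregivers (guide headed Appendix Y).** Domain 2 asks "In your experience, what sources have been most successful at treating these different illnesses". MSC is domain 3.
- **CHWs (guide headed Appendix X).** MSC is the first question.

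The X and Y headings on the two focus group guides are reversed against the appendix list in section 10, so these guides are identified here by participant group.

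**The concern.** The value of MSC lies in letting respondents say what mattered to them before the interviewer says what the study is about. If the programme or its components have just been named, a respondent may offer them back as the most significant change, and the analyst cannot tell an echo from a spontaneous answer. If the question is not asked, that group contributes nothing by the method the protocol assigns to unexpected impacts.

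Both faults bear on secondary objective 4, and neither can be repaired once the interviews are done. Section 5.1 schedules interviews and focus groups for about 9 to 12 months after roll-out, so the guides can be edited before use.

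**Working it through.** No formula applies. The check sets each of the five interview and focus group guides beside the rule in section 4.5.2. Maximum numbers come from section 5.3.3 and Table 4.1.

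| Guide | Max. number | What precedes MSC | Position of MSC | Before direct impact domains? |
|---|---|---|---|---|
| Implementers, App. Q | 5 interviews | (intervention named in introduction) | absent from domains 1 to 8 | not applicable |
| HFI health workers, App. R | 10 interviews | PRIME named and four activity areas listed in introduction; neutral questions on role | domain 2 | yes |
| Stakeholders, App. S | 10 interviews | two items on the job, then 1c naming the PRIME intervention | domain 2 | yes |
| Primary caregivers | 8 focus groups | common illnesses; sources of treatment | domain 3 | yes |
| CHWs | 8 focus groups | introduction only; PRIME not named | domain 1 | yes |

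**Implementers.** The nearest items are 2b, which probes for things participants had not expected, and 3d, which asks which component was implemented most successfully. The first is a second-hand view of other people's expectations; the second is confined to the intervention. Neither is an open question about change. Since section 4.5.1 uses these interviews for hypothesised impacts, the rule in 4.5.2 covers them.

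**HFI health workers.** This is the clearest cue. Before any question, the script also says that the team wants to know whether better services at the centre have improved children's health. Domain 1 is a neutral warm-up; MSC follows, ahead of the domains on training, management and patient-centred services.

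**Stakeholders.** One item names the intervention immediately before MSC. Changes in HFI components come in domain 3, and attribution to PRIME is raised only after that. Item 1c therefore runs against the guide's own progression from open to specific.

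**Caregivers.** Neither the introduction nor domains 1 and 2 name PRIME or the HFI. The departure is one of position, with a general cue about places of care.

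**Counts.** Missing MSC data: up to 5 interviews. MSC asked after PRIME has been named: 10 + 10 = up to 20 interviews. Together these are 5 + 20 = 25, the planned maximum of in-depth interviews. Position only: 8 of the 8 + 8 = 16 focus groups, of which Table 5.3 places 4 in standard care areas.

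**The case against.** The strongest reply is that the substance of the rule is kept. In the health-worker, stakeholder and caregiver guides, MSC comes before the direct questions on hypothesised impacts, which is the sequence section 4.5.2 most needs. That section does not forbid naming the programme, and it describes MSC as a tool for people involved in one. HFI health workers were the targets of the training and implementers delivered it, so naming it may add little. This stands, and it limits the point to the place at the start and, in Appendices R and S, to the cue.

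A reader might go further and infer that four of five guides break the order and that secondary objective 4 therefore leans towards the intervention. The documents do not support that, for four reasons.

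- Pooling the four guides mixes an omission (Q), a clear cue (R), a single-item cue (S) and a matter of position (caregivers).
- The caregiver guide does not name PRIME before MSC, and half of its groups are in standard care areas.
- The health-worker semi-structured questionnaire (Appendix U, up to 10 per arm) opens with an MSC-type sequence in both arms, ahead of its PRIME-specific Part 2.
- Nothing in the documents gives the size of a prompting effect.

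The questionnaire does not close the gap. It reaches neither implementers nor stakeholders, and section 4.5.2 assigns MSC to focus groups and in-depth interviews. Item 2b in Appendix Q may yield something on unexpected effects, but not by the stated method.

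**Conclusion.** The inconsistency between section 4.5.2 and the guides is real and should be reconciled before the interviews begin. As written, MSC data would be missing from up to 5 implementer interviews, and up to 20 further interviews carry a risk of cueing: clear in Appendix R, weaker in Appendix S. The caregiver guide is a minor departure in order across 8 focus groups; the CHW guide complies.

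This rests on two assumptions: that interviewers follow the printed order, and that 4.5.2 applies to every in-depth interview and focus group used for the impact evaluation. The size of any cueing cannot be derived from the documents, and no direction of bias in the answer to objective 4 has been demonstrated.

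**What to change.** - **Appendix Q:** add the three MSC questions (what changed, why it matters, what difference it makes) at the start, before the implementation domains.
- **Appendix R:** move the list of PRIME activities out of the introduction to a point after the MSC domain.
- **Appendix S:** move item 1c to after the MSC domain.
- **Caregiver focus group guide:** make MSC the first domain, for consistency with section 4.5.2 and the CHW guide.

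The cost is editing and reprinting four topic guides and a few extra minutes in up to 5 implementer interviews. No interviews or participants are added. Some prompting will remain, because the consent discussion describes the project and the introductions still convey its subject; in Appendix Q the introduction names the intervention. The report should say so when it presents the MSC accounts.

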## 5 STUDY PROCEDURES

### 5.1. OVERVIEW

The ACT PROCESS study proposed here will be implemented in parallel with the ACT PRIME study, but will be carried out by a different team of field researchers. Self-filled questionnaires, health worker communication assessments and patient exit interviews, IDIs and semi-structured questionnaires, FGDs, and a contextual record will be used to evaluate the process, context and impact of the HFI in the ACT PRIME study. The self-filled questionnaires will be used to evaluate the HFI training and will be conducted during the HFI roll-out period in March-May 2011. The health worker communication assessments and patient exit interviews will be conducted immediately before and after the HFI training in patient-centered services, and then approximately six months following the training for a total of three cycles. The IDIs and semi-structured questionnaires, and FGDs will be conducted approximately 9-12 months after the HFI roll-out. The structured contextual record will be completed by the study team at three-monthly intervals. The timelines for the process, context and impact evaluations in relation to ACT PRIME are outlined in the study procedures timeline below.

**Figure 5.1 Study procedures overview**

[figure not shown]

## 5.2. STUDY SITE

ACT PROCESS, in parallel with ACT PRIME, will be conducted in Tororo district, an area with very high malaria transmission intensity. The estimated entomologic inoculation rate (EIR) in Tororo is 562 infective bites per person-year, and the prevalence of parasitemia among children aged 5-9 years is 63.5% [42-43]. The five sub-counties of West Budama North Health Sub-district (Nagongera, Paya, Kirewa, Kisoko, and Petta), and two sub-counties of West Budama South Health Sub-district (Mulanda and Rubongi) will be included in the study population (Figure 5.2).

**Figure 5.2 Study area**

[figure not shown]

The results of our formative research suggest that this area is very rural, with limited infrastructure and education. Very few households have electricity (1%) and one-quarter have no toilet facilities. One-quarter of the heads of household have received no formal education, and only 21% have received any secondary or higher education [31].

